### Study design

The TRACK-OA study will be carried out at the Arthritis Research Canada (Richmond, BC, Canada) and the Mary Pack Arthritis Centre (Vancouver, BC, Canada). Participants will be recruited from the community in the Greater Vancouver Area. The study is a two-group pilot randomized controlled trial (RCT) with a stepped-wedge design. The stepped-wedge is a trial design in which all participants receive the intervention but the time point at which the intervention is received is randomized (immediate, or after a 5-week delay) (see Fig. 1 for trial flowchart). After receiving informed consent from the participants, baseline measures will be collected.

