#### Assessments

Assessment of outcome measures will occur at three time points—baseline (T0), week 5 (T1), and week 10 (T2)—with the exception of demographic information (collected at baseline only) and adverse events (collected at T1 and T2 only). Both the KOOS and PIH will be uploaded to an online survey system hosted on a secure local server at Arthritis Research Canada, and the SenseWear armbands will be delivered to participants prior to each data collection week.

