#### Randomization

Once informed consent is received and baseline measures have been collected, participants will be randomly assigned to one of two groups (immediate-intervention group or delayed intervention group). As per the stepped-wedge design, the delayed-intervention group will receive the intervention after a 5-week waiting period (i.e. immediately following T1 follow-up assessment; see Fig. 2). A study statistician ([name]) not involved in the day-to-day operation of the trial will randomly assign participants in blocks to each group using a computer-based random number generator and a 1:1 allocation ratio. Block sizes will be concealed from study staff and randomly varied to prevent prediction of group allocation. The statistician will pass group allocations back to study research coordinators (CC, NG) who will arrange for intervention delivery as appropriate. Group assignments will be accessible only to the study research coordinators.

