##### Fitbit flex

Following the education and training session, participants will be asked to wear the Fitbit 24 h/day (unless charging) for the remainder of the study. The Fitbit Flex is a removable tracker (housing a triaxial accelerometer and five-light LED display) inside of a wristband worn on the non-dominant wrist. The Fitbit user-interface is an easy-to-use web-based application that graphically displays a user’s activities over the course of the day including total steps taken, calories burned, and distance traveled. Interaction with the user-interface may occur on a self-directed basis.

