#### Statistical analysis

Descriptive measures will be tabulated and summarized by count, percentage, or mean, and 95 % CI and compared for differences between groups. Integrity of the randomization process will be monitored. SenseWear armband measurements for each time point will be considered valid if they include at least 4 days with at least 20 h of wear time each day [50]. Feasibility data will be collated and compared against benchmarks for success. When assessing preliminary intervention efficacy, the stepped-wedge design allows for analyses of differences between groups as well as temporal patterns. Changes in bouted MVPA, bouted sedentary time, KOOS score, and PIH score will assessed by a multiple regression model including variables for group, time, and group-time interaction. The effect of blocking will be considered in the analysis. Planned comparisons will be used to compare group means for differences at first follow-up (week 5) and to test for a delay effect and for temporal changes intervention efficacy. All analyses will be conducted using IBM SPSS Version 20 (Armonk, NY, USA).

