## Discussion

This paper presents a pilot RCT protocol to assess the feasibility of an intervention designed to increase MVPA and decrease sedentary time in a sample from the knee OA population. The program guides participants in setting personally relevant activity goals based on their preferences and level of ability and slowly increase PA participation over time. It is hoped that this patient-centered approach of gradually integrating greater activity into one’s existing life framework may enhance adherence to PA over time, a recognized challenge [6]. A potential limitation of this intervention is the technological skill requirement, which could act as a barrier to some individuals. However, there are several strengths. First, the use of the stepped-wedge trial design preserves the integrity of a randomized experiment while not withholding a potentially beneficial intervention from study participants. Conventional cross-over designs are impractical for PA promotion interventions as washout-period lengths have not been established and may be of considerable duration. Furthermore, the stepped-wedge design allows for assessment of lag-time effects, which may be relevant for people with arthritis as they may experience delays in the delivery of care. Piloting this trial format will be important in determining any feasibility challenges (e.g. delayed-group participant dropout) that may need addressing in future studies. Second, there is evidence to suggest the emphasis on action-oriented behavioural strategies for PA promotion may be more effective than cognitive or educational methods [24]. Third, the enhanced ability for participants to self-monitor goal progress and receive ongoing feedback that comes through the use of an activity tracker may increase awareness of PA behaviour and enhance activity-related self-efficacy, a known determinant of PA [51]. Fourth, the sharing of Fitbit data between participants and study physiotherapists encourages accountability and provides an opportunity to deliver more specific and personally relevant follow-up support to participants throughout the study. The feasibility metrics such as recruitment rate, dropout rate, adherence, and resource requirements collected in this study will be used to estimate the time, resources, and sample size required for a full-scale RCT. Furthermore, the experience gained from executing study protocols and the feedback provided from staff and participants will allow for improvement and refinement of trial elements and procedures to ensure the success of a future study to test the efficacy of this intervention. Pending the results of this pilot study, a full-sized trial will be designed and conducted in the Greater Vancouver Area in late 2015 and early 2016.

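### The week-10 data cannot separate a delay effect from temporal change in efficacy without a stated period assumption, yet the article plans to test both

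*Protocol article*

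**What the plan says.** All references are to the protocol article.

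- **Study design:** "all participants receive the intervention but the time point at which the intervention is received is randomized".
- **Assessments:** outcomes are measured at weeks 0 (T0), 5 (T1) and 10 (T2).
- **Randomization:** "the delayed-intervention group will receive the intervention after a 5-week waiting period (i.e. immediately following T1 follow-up assessment".
- **Fitbit flex and Telephone follow-up:** after the training session, "participants will be asked to wear the Fitbit 24 h/day (unless charging) for the remainder of the study". The weekly calls cover only the first four weeks of the intervention. At week 10 the immediate group therefore still has the tracker but no longer has the calls.
- **Statistical analysis:** a regression on group, time and their interaction (coding of time not given), with planned comparisons of group means at week 5 and further comparisons "to test for a delay effect and for temporal changes intervention efficacy". Neither of these last two contrasts is defined, and no assumption about period change is stated.
- **Discussion:** as a strength, "the stepped-wedge design allows for assessment of lag-time effects". The reason given is that people with arthritis may have to wait for care.

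**The concern.** The article credits the design with answering two questions beyond week-5 efficacy: whether the effect changes with time, and whether waiting alters it. Both rely on week 10, when both groups have been treated. A delay effect needs the delayed group's response free of whatever else changed between weeks 5 and 10. A temporal change needs the same for the immediate group. No concurrent untreated group supplies that period change.

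Two misreadings are at stake. A week-10 difference near zero could be reported as no decay and no loss from waiting, when equal amounts of each would give the same result. A week 5-to-10 change in the immediate group could be credited to the intervention when it reflects repeat measurement, natural course or season.

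**Working it through.** The article gives no effect size, SD or power for this pilot, so there is no figure to reproduce. The question is which quantities the six group-by-time means can identify.

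**Parameters.** Baseline mean μ, equal in both groups by randomisation. Period shifts from baseline p1 (week 5) and p2 (week 10), with π = p2 − p1. Immediate group's effect at week 5, θ. Change in that group's effect by week 10, m (temporal change). Delayed group's effect at week 10 minus θ, d (delay effect).

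| Group | Week 0 | Week 5 | Week 10 |
|---|---|---|---|
| Immediate | μ | μ + p1 + θ | μ + p2 + θ + m |
| Delayed | μ | μ + p1 | μ + p2 + θ + d |

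**Contrasts.**
1. Week 5, immediate − delayed = θ. Clean.
2. Week 10, immediate − delayed = (p2 + θ + m) − (p2 + θ + d) = m − d. The period shift cancels; m and d do not separate.
3. Immediate group, week 10 − week 5 = m + π.
4. Delayed group's gain (weeks 5 to 10) − immediate group's gain (weeks 0 to 5) = (θ + d + p2 − p1) − (θ + p1) = d + [(p2 − p1) − p1].

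**Rank check.** The design matrix has rank 5 for 6 parameters. μ, p1 and θ are estimable; m, d and p2 are not. Adding 1 to both m and d and subtracting 1 from p2 leaves every cell mean unchanged. Any one restriction restores full rank (5 of 5): p2 = p1, p2 = 2·p1 (equal change in both intervals), d = 0 or m = 0. A hypothetical untreated cell at week 10 would also do so (6 of 6).

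**Illustration.** Take θ = 48 min/week, borrowed from the Background's meta-analysis of chronically ill populations purely for scale, with μ and p1 set to 0.
- Scenario A: m = 0, d = 0, p2 = 0. Immediate (0, 48, 48); delayed (0, 0, 48).
- Scenario B: m = −24, d = −24, p2 = +24. Immediate week 10 = 24 + 48 − 24 = 48; delayed week 10 = 24 + 48 − 24 = 48.

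All six means agree, so no analysis of these means can tell the scenarios apart. The 24 is arbitrary.

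**Size of the error if period change is ignored.** Assume 18 per group (36 at 1:1), equal SDs, within-person correlation ρ of 0.5 to 0.7, normal approximation, two-sided 5%. For contrast 3 with true m = 0, SE = √(2(1 − ρ))/√18 in SD units, which is 0.236 at ρ = 0.5 and 0.183 at ρ = 0.7. The false-positive rate is 1 − Φ(1.96 − π/SE) + Φ(−1.96 − π/SE). For contrast 4 with true d = 0, SE = √(2(1 − ρ))·√(2/18), and the shift is the difference in period change between the intervals.

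| Shift (SD) | Contrast 3 | Contrast 4 |
|---|---|---|
| 0.2 | 14–20% | 9–12% |
| 0.3 | 25–38% | 15–21% |
| 0.5 | 56–78% | 32–49% |

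The documents give no estimate of the shift; these rows are a range, not a forecast.

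**Precision at week 10.** A between-group contrast reaches 80% power only at (1.96 + 0.84)·√(2/18) ≈ 0.93 SD, before baseline adjustment. A null m − d would be weak evidence even without the aliasing.

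**The case against.** The strongest reply is that the article never defines its delay effect. Since the Discussion's motive is people waiting for care, the natural meaning is practical: does starting five weeks later leave people different at week 10? The randomised week-10 contrast answers that without bias. This stands, and on that reading the lag-time sentence is defensible. It does not rescue the plan to test temporal change as a second, separate quantity, because the only randomised week-10 information has then been used.

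It can also be said that contrast definitions belong in a fuller analysis plan. That is fair for the definitions, but no definition separates m from d without an added restriction. Staggered entry (recruitment opened in February 2015 and was expected to reach its target in August) might let calendar season be partly modelled. It would not remove effects of time since enrolment, such as repeat measurement.

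Three stronger readings are tempting and unsupported:
- *A null week-10 difference might be seasonal drift.* Both groups are measured at the same study time, so a common period shift cancels in m − d.
- *The group-time interaction is not a treatment effect.* With time as a factor, the group-by-week-5 term is the week-5 effect. If group differences run 0, θ, 0, the interaction vanishes only when time is a single linear term (−1·0 + 0·θ + 1·0 = 0). The article does not state that coding, and its planned week-5 comparison of means points away from it.
- *Efficacy itself is compromised.* The week-5 comparison is named separately and is intact.

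Continued tracker use at week 10 is stated openly, and the article makes no claim of clean post-intervention maintenance. It bears only on how m is described.

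**Conclusion.** The concern holds in a limited form. With two groups, three visits and no untreated group at week 10, delay effect and temporal change cannot each be estimated unless one restriction is stated, and the article states none. The non-identifiability follows from the layout alone and assumes only equal baseline means by randomisation and a period shift common to both groups. The error rates rest on the assumed shift, correlation and group size.

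The consequence is moderate. These are exploratory comparisons in a 36-person pilot without a power calculation, and the week-5 contrast, the natural effect estimate for sizing the later two-group trial, is unaffected. It is still worth correcting, because a within-group week 5-to-10 test would attribute uncontrolled period change to the intervention.

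**What to change.** 1. Enter time as a factor and take efficacy from the week-5 between-group contrast, adjusted for baseline.
2. Define the week-10 between-group contrast as immediate versus delayed start, and state that it combines delay with time since start.
3. Report week 5-to-10 within-group changes and cross-time comparisons as descriptive, or as conditional on a named assumption: no period change from week 5 to week 10, or equal period change in the two intervals.
4. Qualify the statements in Statistical analysis and Discussion to match. For example, say that the design compares early with delayed start at week 10, and that separating delay from change over time needs one of those assumptions.

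The cost is analysis labelling and wording, plus one advertised inference given up. No visit, participant or measurement changes. An untreated group through week 10 would identify everything, but it would be a different design from one in which everyone is treated and is not proposed here.

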#### Dissemination and knowledge translation

Patient collaborators from the Arthritis Research Canada’s Arthritis Patient Advisory Board (APAB) were consulted during the study design process to provide insight into patient values and concerns regarding physical activity and use of wearable activity trackers. Open channels of communication will be maintained with APAB during the study for patient perspectives on challenges or changes to study protocol. Study results will be featured on the Arthritis Research Canada website, as well as the lab website hosted through the University of British Columbia. Furthermore, results will be disseminated through the Arthritis Research Canada monthly e-newsletter and through a presentation at an APAB monthly meeting. Results will be shared with the scientific community by way of publication and conference presentation.

## Discussion

This paper presents a pilot RCT protocol to assess the feasibility of an intervention designed to increase MVPA and decrease sedentary time in a sample from the knee OA population. The program guides participants in setting personally relevant activity goals based on their preferences and level of ability and slowly increase PA participation over time. It is hoped that this patient-centered approach of gradually integrating greater activity into one’s existing life framework may enhance adherence to PA over time, a recognized challenge [6]. A potential limitation of this intervention is the technological skill requirement, which could act as a barrier to some individuals. However, there are several strengths. First, the use of the stepped-wedge trial design preserves the integrity of a randomized experiment while not withholding a potentially beneficial intervention from study participants. Conventional cross-over designs are impractical for PA promotion interventions as washout-period lengths have not been established and may be of considerable duration. Furthermore, the stepped-wedge design allows for assessment of lag-time effects, which may be relevant for people with arthritis as they may experience delays in the delivery of care. Piloting this trial format will be important in determining any feasibility challenges (e.g. delayed-group participant dropout) that may need addressing in future studies. Second, there is evidence to suggest the emphasis on action-oriented behavioural strategies for PA promotion may be more effective than cognitive or educational methods [24]. Third, the enhanced ability for participants to self-monitor goal progress and receive ongoing feedback that comes through the use of an activity tracker may increase awareness of PA behaviour and enhance activity-related self-efficacy, a known determinant of PA [51]. Fourth, the sharing of Fitbit data between participants and study physiotherapists encourages accountability and provides an opportunity to deliver more specific and personally relevant follow-up support to participants throughout the study. The feasibility metrics such as recruitment rate, dropout rate, adherence, and resource requirements collected in this study will be used to estimate the time, resources, and sample size required for a full-scale RCT. Furthermore, the experience gained from executing study protocols and the feedback provided from staff and participants will allow for improvement and refinement of trial elements and procedures to ensure the success of a future study to test the efficacy of this intervention. Pending the results of this pilot study, a full-sized trial will be designed and conducted in the Greater Vancouver Area in late 2015 and early 2016.

## Trial status

The trial began recruitment in 20 February 2015 and is presently open for recruitment. Recruitment will close when 36 participants have been randomized. It is anticipated this target will be met in August 2015.

## Abbreviations

BMI: body mass index
CI: confidence interval
KOOS: Knee Injury and Osteoarthritis Outcome Score
MET: metabolic equivalent
MVPA: moderate-to-vigorous physical activity
OA: osteoarthritis
PA: physical activity
PIH: partners in health scale
